## 291    **Statistical methods**

292        The analysis of the primary (depressive symptoms at three months) and secondary (depressive  
 293    symptoms at five months, proportion of clinically significant depressive symptomatology - PHQ-9 $\geq$ 10, and  
 294    anxiety, loneliness, quality of life and capability well-being at three and five months) outcomes will follow  
 295    the intention-to-treat (ITT) principle, i.e. participants will be analysed in the arm to which they were allocated  
 296    (regardless of adherence to the intervention), and will follow the Consolidated Standards of Reporting Trials  
 297    (CONSORT) guidelines for randomised trials [42]. No interim analyses are planned. Descriptive statistics will  
 298    compare differences in baseline demographics and clinical characteristics between the intervention and  
 299    control arms to identify any imbalances. Linear regression models adjusted for stratification and the relevant  
 300    baseline score will be used to examine the primary and secondary continuous outcomes. For the binary  
 301    outcome, logistic regression and Poisson regression models will be used to generate relative risks. For  
 302    secondary analyses, models will include any baseline variables that are not balanced between arms.

303        Exploratory subgroup analyses will include the Wald test for interaction terms between the relevant  
 304    baseline variable and trial allocation in the above regression models to examine whether baseline PHQ-9  
 305    scores, gender, age, education level, and comorbid physical illness (diabetes, hypertension, and both) modify  
 306    the effect of the intervention on PHQ-9 scores at both follow-ups. The results of these analyses will need to  
 307    be interpreted with caution due to the limited power to detect such interactions and the paucity of evidence  
 308    on the theoretical basis for these hypotheses.

309        Additional analyses will include a Complier Average Causal Effect (CACE) analysis [43] using an  
 310    instrumental variable estimator and imputed data to determine the effect of the number of messages  
 311    listened to, on the reduction in depressive symptom severity at both three and five months. At the three-  
 312    month follow-up, participants randomised to the intervention arm will be asked at the end of the assessment  
 313    how many messages they listened to from start to finish, with the following options: *none, a few, at least*  
 314    *half, most or all*. The CACE analysis will consider listening to at least *most* of the messages received as the  
 315    threshold, as we hypothesise that this is the minimum number of messages that participants need to listen  
 316    to in order to have a therapeutic effect. Alternative analyses will be conducted using the thresholds of (a)

317 listening to at least half of the messages and (b) listening to all of the messages. We will also consider using  
 318 the number of messages opened (as recorded by the system) as a continuous variable (if assumptions of  
 319 linear relationships are met).

320 If we find any marked differences in missing data between the intervention and control arms, or a  
 321 proportion of missing data greater than 10%, then we will impute missing data separately for each arm for  
 322 all analyses described above. We will use multiple imputations by chained equations (MICE models),  
 323 assuming data are missing at random (MAR) [44]. MICE models will include variables from the original  
 324 analyses (outcomes, stratification and gender) and any other variables that predict missingness [45,46]. The  
 325 selection model approach will be used to conduct sensitivity analyses testing for modest departures from the  
 326 MAR assumption for primary outcomes only [47–49].

327 The cost-effectiveness analysis will compare the costs and effects of the Viva Vida programme against a  
 328 single message from the health system's perspective. The first analysis will estimate the incremental cost-  
 329 effectiveness using (a) the primary clinical outcome measure (cost per patient recovered), and (b) the quality  
 330 adjusted life years (QALYs) calculated using the EQ-5D-5L [36,50]. Incremental cost-effectiveness ratios and  
 331 cost-effectiveness acceptability curves will be presented to show the probability of the intervention being  
 332 cost-effective at a range of willingness-to-pay thresholds [36,50]. The second analysis will be the Net  
 333 Monetary Benefit (NMB) statistic; it will be calculated at the WHO recommended threshold for LMICs using  
 334 the difference in costs and the difference in QALYs between the two arms. The EQ-5D-5L responses will be  
 335 converted to utility scores using the most appropriate population tariff for the Brazilian population available  
 336 at the time of the analysis. QALYs will be estimated using utility scores adjusted for baseline values. We will  
 337 use national, where available, or local unit costs to value resource use.

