## 185 Sample size

186 To detect what we consider to be a relevant clinical difference between the two randomised arms of  
187 0.33 standard deviations [14], 142 to 162 individuals in each arm gives 80% to 85% power at a two-sided 5%  
188 significance level. Data from our PROACTIVE pilot study [38] (PHQ-9 means of 5.9 and 6.4 with a standard  
189 deviation of 1.5; data not published) suggest that this effect size is feasible for this kind of intervention. We  
190 anticipate 25% attrition and therefore plan to recruit 225 individuals in each arm, for a total sample size of  
191 450.

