## 192 Recruitment

193 The Guarulhos Health Secretariat will provide a list with contact details of all individuals aged 59 years  
 194 or older who are registered in the participating UBSs (the slightly lower age limit compared to the relevant  
 195 inclusion criterion is so that we include individuals who would be 60 years old during the recruitment period).  
 196 Names duplicated on the list, individuals without a mobile phone number, and participants from our previous  
 197 RCT conducted in Guarulhos [24] will be excluded. The remaining individuals (alphabetical ordered) on the  
 198 list will receive a random ID number. The recruitment will follow the ID number in ascending order. This new  
 199 list will be used to simultaneously recruit participants for two RCTs evaluating a digital intervention for older  
 200 adults with depressive symptoms being conducted by our research group [39]. These two studies will use the  
 201 same protocol to recruit participants; only the inclusion criterion for the severity of depressive symptoms  
 202 will be different. In the present study, we will recruit older adults with subthreshold symptoms of depression  
 203 as defined above.

204 The research team will contact via WhatsApp message individuals who have at least one mobile phone  
 205 number. This message will briefly describe the study and inform these individuals that a research assistant  
 206 will contact them by phone. Only those whose WhatsApp message is successfully delivered (i.e. an active  
 207 WhatsApp number) will be contacted by phone and invited to start the recruitment interview. This interview  
 208 will consist of three stages:

- 209 (a) Screening assessment: will assess inclusion criteria (age, WhatsApp use and assessment of depressive  
 210 symptoms) and exclusion criteria (communication and engagement problems, acute suicide risk, and health  
 211 conditions that prevent participation in the trial);
- 212 (b) Baseline assessment: participants screened positive for subthreshold depressive symptoms and with no  
 213 exclusion criteria will be assessed for anxiety, loneliness, quality of life, capability well-being, socioeconomic  
 214 profile (marital status, race, education level, living arrangement, and personal and household income), and  
 215 alcohol and tobacco use;
- 216 (c) Invitation to participate in the study.

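### Extra covariates for the secondary analyses are chosen by observed baseline imbalance rather than fixed in advance for prognostic value; the error is conservative and leaves the primary model untouched

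*Protocol*

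**What the plan says.** All of this is in the protocol.

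- **Main models (Statistical methods).** Primary and secondary continuous outcomes are examined with "Linear regression models adjusted for stratification and the relevant" baseline score. This part is prespecified.
- **Baseline comparison (same section).** Descriptive statistics will "compare differences in baseline demographics and clinical characteristics between the intervention and" control arms, with the stated aim of finding imbalances.
- **Selection rule (same section).** For secondary analyses, "models will include any baseline variables that are not balanced between arms".
- **Variables available (Recruitment).** People who screen positive and have no "exclusion criteria will be assessed for anxiety, loneliness, quality of life, capability well-being, socioeconomic" profile and alcohol and tobacco use. Counted singly, 12 of these variables lie outside the main PHQ-9 model: anxiety, loneliness, quality of life, capability well-being, marital status, race, education, living arrangement, personal income, household income, alcohol and tobacco.

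The text does not say whether secondary analyses means analyses of the secondary outcomes or further-adjusted models of all outcomes, including three-month PHQ-9.

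**The concern.** Allocation is individual, in stratified random permuted blocks, so any baseline difference beyond the stratification factors is chance. A covariate earns its place in an adjusted model by predicting the outcome. Observed imbalance is a different property and carries no information about prediction. Choosing on it has three consequences:

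1. A strong predictor is left out whenever it happens to be balanced, so available precision is not used.
2. The unadjusted standard error reported in that case is too large. It describes the spread over all possible allocations, yet the model is used only where the predictor was found balanced, and there the estimate varies less.
3. The model is known only after the arms have been compared, so it is not a prespecified analysis.

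At stake are the precision, the calibration and the prespecified status of the secondary analyses.

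**Working it through.** **1. The plan's own sample size.** Inputs from Sample size: effect 0.33 SD, two-sided 5%, 80% to 85% power, 1:1 allocation. The formula is n per arm = 2(z₀.₉₇₅ + z_power)² / d².

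- d = 0.33: 2 × (1.960 + 0.842)² / 0.1089 gives 145; with 1.036 in place of 0.842 it gives 165.
- d = 1/3, the pilot ratio (6.4 − 5.9)/1.5: 142 and 162, exactly as stated.
- Attrition of 25%: 162/0.75 = 216 and 165/0.75 = 220, both covered by the planned 225.
- Expected analysed: 225 × 0.75 = 168.75, taken as 168 per arm. Power at 0.33 SD with no extra covariate is then about 86%.

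The sample size reproduces and does not depend on the selection rule.

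**2. How often chance alone flags a variable.** The 0.1 threshold is an assumption. With 225 per arm, SE of a standardised difference = √(2/225) = 0.094, so P(|Z| > 0.1/0.094) = 0.289. Over 12 variables that is 12 × 0.289 = 3.5 expected flags. With a p<0.05 criterion, and if the 12 were independent (they are probably not), P(at least one) = 1 − 0.95¹² = 0.46.

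**3. Why the standard error is too large.** Let r be the covariate's correlation with the outcome after the prespecified terms, in units of residual SD.

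- Reported when the covariate is left out: √(2/168) = 0.109.
- Actual spread if the covariate is exactly balanced: √(2(1 − r²)/168). At r = 0.5 this is √(2 × 0.75/168) = 0.0945.
- Ratio: 0.109/0.0945 = 1.15, so the reported value is about 15% too large in that limiting case.

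**4. Simulation, one candidate covariate, 168 per arm, true effect 0.33 SD.** Ranges reflect separate runs. The power gap is measured against always including the covariate.

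| Rule | r | Type I error | Power gap |
|---|---|---|---|
| Standardised difference > 0.1 | 0.5 | about 3.8% | about 4 points (89% v 93%) |
| Standardised difference > 0.1 | 0.3 | 4.4% to 4.8% | about 1.5 points |
| p < 0.05 | 0.5 | below 5% | about 6 to 8 points |
| p < 0.05 | 0.3 | below 5% | about 3 points |

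**5. Simulation, ten candidates of which three are prognostic.** R² is the share of residual outcome variance that the three explain together. There were 20,000 null and 8,000 alternative replicates per scenario.

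| R² | Size, 0.1 rule | Power, 0.1 rule | Size, p<0.05 rule | Power, p<0.05 rule | Power, prespecified |
|---|---|---|---|---|---|
| 10% | 4.7% | 86% | 4.7% | 86% | 89% |
| 20% | 4.1% | 89% | 4.5% | 86% | 92% |
| 30% | 3.6% | 90% | 4.3% | 86% | 94–95% |
| 50% | 1.9% | 94% | 3.6% | 87% | 99% |

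At R² = 30% under the 0.1 rule, the mean reported SE was 0.1042 against a true spread of 0.0966. With prespecified covariates the two agreed (0.0916 against 0.0925), and size stayed between 4.6% and 5.4% in all scenarios. With no extra covariates, power was about 85% to 86%.

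The correlations, R² values, number of prognostic variables and thresholds are all assumptions; the protocol gives none of them. The simulations cover continuous outcomes only.

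**The case against.** The strongest reply is that the models carrying the inference are already fixed. Stratification factors and the relevant baseline score enter the linear models whatever the balance, and the baseline score is an obvious candidate predictor. On that view the disputed sentence adds a supplementary check for chance imbalance, and such a check does not exist to maximise power. The simulations support part of this: power under the rule is no lower than with no extra covariates (about 85% to 86%), so the rule gains less than it could but loses nothing against the main model. Selection also uses baseline data, not outcomes, which limits the scope for steering a result. These points stand and they limit the size of the defect. They do not remove it: the sentence states a method, that method is inferior to a prespecified list, and its scope is unclear.

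Three stronger readings are tempting, and the documents do not support them.

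- **That the rule inflates false positives.** It does the reverse: type I error falls below 5%.
- **That the missing threshold for imbalance is itself a fault.** Such detail is commonly left to the statistical analysis plan, which the protocol says exists and which is not at hand. A threshold there would still leave selection by imbalance in place.
- **That the choice is made by an analyst who knows the arms.** The protocol describes only a descriptive comparison, which could be done with coded arms.

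**Conclusion.** The point holds for the secondary analyses. The protocol fixes a covariate rule based on observed imbalance, which is unrelated to prognostic value and yields a model known only after the arms are compared. A reader might infer that the primary result or the sample size is at risk. Neither is: the main linear models are prespecified and the sample size reproduces. The qualification is scope. If secondary analyses includes a further-adjusted model of three-month PHQ-9, the rule would produce a second, data-chosen estimate beside the primary one.

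The error is conservative and modest. With one covariate and a 0.1 threshold, type I error is about 3.8% at r=0.5 and 4.4% to 4.8% at r=0.3, with power about 4 and 1.5 points below prespecified adjustment. With a p<0.05 criterion the power gaps are about 6 to 8 and 3 points. All of this depends on how much the remaining variables predict beyond the baseline score, which the protocol does not tell us; if they predict nothing, the loss is close to nil. This is an improvement worth making because it is almost free, not a threat to the trial's main conclusion.

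**What to change.** Replace the sentence with a rule along these lines: secondary adjusted models will add a fixed list of baseline covariates, judged prognostic and chosen before the arms are compared, to the stratification factors and the relevant baseline score, regardless of observed balance.

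- **List.** The trial team should choose it on prior knowledge. GAD-7, the 3-item UCLA scale and education level are examples from variables already collected; the protocol itself gives no evidence on how well they predict.
- **Scope.** State whether the rule applies to the secondary outcomes, to further-adjusted models of all outcomes, or to both.
- **Baseline table.** Keep the comparison of arms descriptive, with no role in model choice.
- **Timing.** Oversight and monitoring says the steering committee will receive reports on balance between the arms. If these cover baseline variables, the list should be set by people who have not seen them.

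The cost is a change of wording and a few degrees of freedom out of about 336 analysed participants (2 × 168). No new data are needed.

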## 97    **Digital psychosocial intervention**

98            The Viva Vida programme was adapted from the short, animated videos shown by community health  
 99 workers to older adults with depressive symptomatology in the RCT testing the PROACTIVE intervention  
 100 [24,25] and grounded in the theories of psychoeducation [26] and behavioural activation [27]. Behavioural  
 101 activation is an approach in mental healthcare that aims to promote behaviours that activate positive  
 102 emotions, as well as avoid those that worsen depressive symptoms, and integrate them into one's routine  
 103 [27]. The programme consists of 48 messages that will be sent to participants via WhatsApp over six weeks,  
 104 four days per week. Each day, they will receive one message in the morning and one in the afternoon. No  
 105 support of health professionals will be provided as part of the intervention.

106            There are two types of messages: audio messages and images with short texts. Audio messages last, on  
 107 average, three minutes and are based on the storytelling technique, a communication tool that can attract  
 108 attention, arouse emotions and engage listeners to influence their attitudes and beliefs [28]. We chose audio  
 109 messages because of the low level of education and income of the older adults living in disadvantaged areas  
 110 of Guarulhos. The audio messages are short to make Viva Vida viable for older people with mobile phones  
 111 with low storage capacity. Through the audio messages, two fictitious characters ([name] and [name])  
 112 share experiences as if they had participated in the Viva Vida programme. These characters share what they  
 113 have learned about depression (psychoeducation), how they have felt, and what kind of pleasant and  
 114 meaningful activities they have done, and the ones they have avoided to increase positive interactions with  
 115 people and the environment (behavioural activation). The messages also include health promotion tips, such  
 116 as information on diet, physical activity, the importance of other health treatments, and relapse prevention.  
 117 The audio and visual messages advise participants to contact health services if they feel that their depressive  
 118 symptoms are not improving or are getting worse. The characters use language, vocabulary, tone and manner  
 119 appropriate to the target audience. They are realistic to create empathy for the study participants when  

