## 149 **System to deliver the messages**

150 The technical research team will coordinate the delivery of the messages. We will use a web system  
151 integrated with the WhatsApp Business Application Programming Interface (API), which is managed by an  
152 intermediary company. This system is hosted on a cloud service where access is restricted by both  
153 authentication and authorisation processes. Data flowing to and from browsers is also protected through the  
154 use of encryption. The WhatsApp Business API allows the research team to capture the date and time  
155 (timestamp) when messages are sent, delivered and opened, replies to the quick reply tool, and the content  
156 of spontaneous messages. The API enables customised messages (e.g. messages with the recipient's name)  
157 and the attachment of audio and image files. Messages will be scheduled weekly and delivered using a job  
158 scheduler on the server.

159 During the first two weeks of the programme, a member of the technical support team (who does not  
160 take part in the other activities of the study) will contact participants who are not receiving or opening the  
161 messages to check if they are experiencing any technical problem. We will identify these participants through  
162 the Viva Vida web dashboard, which will show the status of messages as *sent to intermediary company*  
163 *platform, sent to participant, delivered to participant, or opened by the participant*. During the remaining  
164 four weeks of the Viva Vida programme, participants will be able to contact the technical support team if  
165 they are not receiving the messages.

166 We will remove participants who block their mobile phones from receiving the Viva Vida messages to  
167 comply with the WhatsApp policy and keep our system functional. These participants will not receive new  
168 intervention messages, but will be contacted again during follow-up evaluations unless they contact us to  
169 withdraw their consent to participate in the study.

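### The main CACE threshold is a share of the messages each participant received but is justified as a minimum number, so an early blocker can count as a complier on less exposure than a non-complier

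*Protocol*

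**What the plan says.** Under Statistical methods, the protocol plans a CACE analysis with an "instrumental variable estimator and imputed data to determine the effect of the number of messages" listened to. Exposure is self-reported. At three months, intervention participants are asked "how many messages they listened to from start to finish, with the following options: *none, a few, at least" half, most or all. The question as described names no denominator.

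The main analysis will "consider listening to at least *most* of the messages received as the" cut-off. The sentence continues: "threshold, as we hypothesise that this is the minimum number of messages that participants need to listen" to for a therapeutic effect. The two alternative cut-offs are "listening to at least half of the messages and (b) listening to all of the messages. We will also consider using" a further exposure measure: "the number of messages opened (as recorded by the system) as a continuous variable", provided linearity holds. The alternatives refer to the messages in general. Only the main cut-off refers to messages received.

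On dose, Digital psychosocial intervention says: "The programme consists of 48 messages that will be sent to participants via WhatsApp over six weeks". The week-by-week programme table splits these into 24 audio and 24 image messages.

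On delivery, System to deliver the messages says: "We will remove participants who block their mobile phones from receiving the Viva Vida messages to" comply with the messaging service's policy. These participants get no new messages but are contacted for follow-up unless they withdraw consent. The same section says that the system logs when each message is sent, delivered and opened.

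**The concern.** The target and the justification both describe an absolute dose: how many messages were heard, and the fewest that could work. The rule is a proportion whose denominator varies between participants. The two agree only if everyone receives the same number of messages, and the protocol itself describes a group that will not.

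Applied as written, the rule can class a person with very little exposure as a complier and a person with several times that exposure as a non-complier. The main threshold then no longer tests the hypothesis given for it. An instrumental-variable estimator divides by the complier proportion, so adding low-dose participants to the compliers also pulls the estimate towards zero.

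**Working it through.** **Programme dose.** 6 weeks × 4 days × 2 messages = 48, which reproduces the protocol's figure. That is 8 messages a week, of which 4 are audio. Over six weeks it is 24 audio and 24 image messages.

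**Which scale applies.** The question asks what was listened to from start to finish, which fits the audio messages. The comparison is therefore made on 24 audio messages, with all 48 as a check.

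**Two participants under the main rule.**

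- A blocks after week 1, has heard everything that arrived, and answers relative to what arrived. Received: 4 audio messages (8 in all). Heard: 4 of 4, so A is a complier. Share of the programme: 4/24 = 8/48 = 17%.
- B is sent everything and hears half: 12 of 24 audio messages (24 of 48 in all). B answers *at least half*, which falls below *most*, so B is a non-complier on the main rule. Share of the programme: 50%.
- Ratio of exposure, B to A: 12/4 = 24/8 = 3.

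*Most* has no numerical definition. If it meant at least 60%, 75% or 90%, a fully supplied non-complier could have heard up to 14, 17 or 21 audio messages, which is 3.5, 4.25 or 5.25 times A's 4.

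**Effect on the estimate (illustration only).** The simple instrumental-variable ratio is CACE = ITT effect / complier proportion. Let p be the complier proportion on the scheduled programme and f the further share of the arm counted as compliers only because the denominator is messages received. The relative change is p/(p + f) − 1. The ITT effect is set at 0.33 SD, the planning difference under Sample size. The protocol gives no compliance or blocking rates, so p and f are assumptions.

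| p | f = 0 | f = 2% | f = 5% | f = 10% |
|---|---|---|---|---|
| 40% | 0.825 | 0.786 (-4.8%) | 0.733 (-11.1%) | 0.660 (-20.0%) |
| 50% | 0.660 | 0.635 (-3.8%) | 0.600 (-9.1%) | 0.550 (-16.7%) |
| 60% | 0.550 | 0.532 (-3.2%) | 0.508 (-7.7%) | 0.471 (-14.3%) |

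For example, 0.33/0.50 = 0.66 and 0.33/0.55 = 0.60.

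**The case against.** **Blocking alone does not make someone a complier.** A reader might infer that everyone who blocks early is counted as a complier. The documents do not support that. The person must have heard most of what arrived, complete the three-month interview, and answer relative to what arrived. Week 1 tells participants how many messages the programme has, so *a few* is a plausible answer. This stands, and it makes f small or unknown. It does not reconcile the rule with its rationale.

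**Only the main threshold says *received*.** A reader might extend the fault to all three thresholds. The wording of the two alternatives does not support that. It does leave the main and alternative thresholds worded on different denominators, which is itself worth correcting.

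**The thresholds stay ordered.** It is tempting to say that dose ordering across the thresholds breaks down. All three come from one ordinal answer, so the complier sets remain nested. What can be misordered is absolute exposure between individuals.

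**The example depends on the scale.** Someone who heard 22 messages looks like a non-complier against 48, but 22 of the 24 audio messages is 92% and plausibly counts as *most*. That example should not be used. The comparison of 4 with 12 audio messages holds on either scale.

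**The protocol has partial safeguards.** Technical support contacts people who are not receiving or opening messages in the first two weeks, and participants can ask for help afterwards. The count of messages opened is an absolute measure on which early blockers would score low. But that analysis is only to be considered, depends on linearity, and leaves the threshold analysis as it is.

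**Detail may sit elsewhere.** Complier classification is often completed in the statistical analysis plan, which the protocol cites and which is not at hand. The point here is a rule the protocol does state, not an omission.

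**Conclusion.** The point holds as an inconsistency within the protocol. The main CACE rule is a share of messages received, its rationale and target are numbers of messages, and the blocking provision guarantees that the two can differ. On the protocol's own schedule a complier can have had one third of a non-complier's exposure.

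Its reach is limited to an additional analysis. A reader might infer that the primary comparison is affected; it is not, because that analysis follows allocation regardless of adherence.

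The size of the shift in the CACE cannot be derived from the protocol. The tabulated changes of about -3% to -20% depend on assumed compliance of 40% to 60% and an assumed 2% to 10% misclassified. They compare the same estimator under two denominators. They do not measure bias against the true effect: the ratio assumes no benefit below the threshold, and if partly exposed participants do benefit, a dichotomised CACE is pushed upwards. The net direction of error is therefore not established.

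**What to change.** In the CACE paragraph, define the main threshold against the scheduled programme instead of messages received, and word alternatives (a) and (b) the same way. If *listened to* refers to audio, the denominator is the 24 scheduled audio messages. Half is then 12 and all is 24, and the authors should state the count they intend by *most*.

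Add a rule that uses the existing log: anyone with too few scheduled messages delivered to reach a threshold is a non-complier at that threshold, whatever they report. Otherwise the self-reported category stands. Word the three-month question to refer to the whole programme if it can still be changed.

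The cost is a sentence or two and one merge with the message log. The complier proportion will be lower and the CACE interval somewhat wider. Treating the standard error as the ITT standard error divided by the complier proportion, moving from 55% to 50% widens the interval by 0.55/0.50 = 1.10, or about 10%.

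Some error remains. A person who blocks after week 4 has had 16 audio messages. If they heard 8 and report *at least half*, they still pass alternative (a) at 8/24 = 33%. The system-recorded count of messages opened can serve as a check on such cases.
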